#### 4.1.4. Outcomes

Outcome measures will be kept to a minimum in accordance with recommendations to reduce participant demand and minimise attrition in studies involving people with ID [38]. A summary of assessments completed online by participants at baseline, immediately post-intervention, and 3-month follow-up is presented in Table 1.

Primary outcome measures: The primary outcome measure will be the Anxiety Depression and Mood Scale (ADAMS) [39]. The ADAMS is a 28-item self-report inventory that provides an assessment of psychiatric symptoms across five domains of pathology: (1) manic–hyperactive behaviour; (2) depressed mood; (3) social avoidance; (4) general anxiety; and (5) obsessive–compulsive behaviour. As both the total ADAMS score and each of the five subfactor scores demonstrate sound validity and reliability [39], efficacy of the intervention will be defined as a significant reduction in either the depressed mood or general anxiety subfactors.

Secondary outcomes: The Kessler-10 (K10) will provide an additional assessment of psychiatric symptoms [26]. The K10 is the standard measure of general psychopathology in the Australian healthcare system and thus will allow population-level comparisons between our sample and the broader Australian community.

The World Health Organisation Disability Assessment Schedule 2.0 (WHO-DAS) will provide a measure of disability and daily functioning [40]. The WHO-DAS is a 36-item self-report measure of measure health and disability across six life domains: (1) cognition; (2) mobility; (3) self-care; (4) getting along with others; (5) daily life activities, such as domestic duties; and (6) participating in society. Domain scores will be computed using the “item–response–theory” method to enable domain-level analysis across time.

Additional measurements: The autism spectrum quotient (AQ) will provide a measure of autism spectrum disorder (ASD) symptoms previously classified in the Diagnostic and Statistical Manual of Mental Disorders (DSM-IV) as characteristic of Asperger’s syndrome [41]. ASD symptoms are common in individuals with ID and may explain treatment effects [42]. The AQ is a 50-item self-report inventory that provides an overall measure of ASD symptom severity and shows excellent discriminant validity from other psychiatric disorders [41].

The CBS Health assessment system will provide an estimate of four key areas of cognitive function: (1) The Digit Span task will provide an estimate of verbal working memory; (2) the Grammatical Reasoning task will provide an estimate of the ability to use verbal information to draw conclusions; (3) the Spatial Planning task will provide a measure of the ability to use visual information to plan ahead; and (4) the Feature Match task will test the ability to focus one’s attention on specific features of an image. (https://www.cambridgebrainsciences.com/).

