## 2. Objectives and Hypotheses

The primary aim of this study is to answer the research question regarding whether using a tailored eMH program (Healthy Mind) can reduce symptoms of anxiety and depression and improve daily functioning in people aged 16-years and over with borderline-to-mild ID. A secondary aim is to examine any effects that specific impairments in intellectual functioning (e.g., poor working memory) may have on engagement with, and benefits of, an eMH program. We predict that people who use the intervention will report reduced depression and anxiety, relative to the control group. We also predict that lower scores on tests of cognitive function will be related to lower engagement and benefit in the treatment group.

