## 6. Sample Size

The primary outcomes for this study are depression and anxiety symptoms (measured using the ADAMS). Meta-analysis of psychological therapies for people with ID suggests an expected effect of treatment on similar measures of anxiety and depression symptoms of approximately 0.6 [43]. However, this is based on face-to-face treatments and may represent an overestimation [44]. To detect a more conservative effect size of ~0.5, we will need a minimum of 50 participants per group, therefore we will recruit a sample of approximately 167 individuals to allow for ~40% attrition. This calculation was based on the group differences on ADAMS between waitlist control and intervention groups at 8 weeks and 3 months, assuming 80% power and alpha = 0.05 (0.025 for each primary group difference), in order to detect a mean difference of 0.5 standard deviation units at 8 weeks and at 3 months.

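### The either-subscale success rule, read with two primary time points, gives four routes to an efficacy claim, while alpha is divided for two

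*Protocol article*

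**What the plan says.** Section 4.1.4 names the ADAMS as the primary outcome measure and then sets the success rule: "efficacy of the intervention will be defined as a significant reduction in either the depressed mood or general anxiety subfactors". The rule attaches no time point.

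Section 6 opens with "The primary outcomes for this study are depression and anxiety symptoms (measured using the ADAMS" and bases the calculation on "group differences on ADAMS between waitlist control and intervention groups at 8 weeks and 3 months". It continues "assuming 80% power and alpha = 0.05 (0.025 for each primary group difference", and closes with "in order to detect a mean difference of 0.5 standard deviation units at 8 weeks and at 3 months". On size it says "we will need a minimum of 50 participants per group", raised to about 167 recruited for about 40% attrition.

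Section 9.3 gives an intention-to-treat repeated-measures mixed model. It does not state an order of testing, a gatekeeping rule or any other allocation of alpha. Neither Section 4.1.4 nor Section 6 says whether tests are one-sided or two-sided.

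**The concern.** The two sections count the primary tests differently. Section 4.1.4 lets either of two subscales carry the claim. Section 6 makes two time points primary. Together they give four contrasts: depressed mood and general anxiety, each at 8 weeks and at 3 months. A division of 0.05 into two parts pays for two of them. If the parts belong to the time points, as the Section 6 sentence suggests, nothing is set aside for having two subscales. If they belong to the subscales, nothing is set aside for having two times.

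This is not a detail that the article leaves to an analysis plan. The article itself fixes the either-rule, the two primary times and the two-way split, and these do not fit together. At stake is the error rate behind the trial's efficacy claim.

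**Working it through.** **Inputs from the protocol article.** Two subscales, either sufficient (4.1.4); two time points, overall alpha 0.05, 0.025 per difference, 80% power, effect 0.5 SD, 50 per group, about 40% attrition, 167 recruited (6).

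**Inputs assumed.** The article gives no correlations. I take 0 to 0.7 between subscales and 0.3 to 0.7 between time points, and look beyond that range as a check.

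**1. The plan's alpha figure.** 2 × 0.025 = 0.05. The split reproduces, for exactly two tests.

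**2. Four tests at 0.025.**
- Bonferroni bound: 4 × 0.025 = 10%.
- If independent: 1 − 0.975⁴ = 9.6%.
- If correlated: simulated four-variate normal test statistics under no effect, with the correlation matrix formed as the product of subscale and time correlations (at least 1,000,000 draws).

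| Correlation, subscale / time | Two-sided 0.025: any rejection | Two-sided 0.025: benefit direction only | One-sided 0.025: benefit direction |
|---|---|---|---|
| 0 / 0.3 | 9.5% | 4.8% | 9.3% |
| 0.5 / 0.5 | 8.6% | 4.3% | 8.1% |
| 0.7 / 0.7 | 7.3% | 3.6% | 6.8% |
| 0.8 / 0.8 | 6.4% | 3.2% | 6.0% |
| 0.9 / 0.9 | 5.2% | 2.6% | 4.9% |
| Bound | 10% | 5% | 10% |

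The first results column is the familywise error in the usual two-sided sense. The other two give the chance of a false claim of benefit, which is what the success rule concerns, under each reading of the unstated sidedness. The benchmark for the middle column is 2.5%, the share of a two-sided 5% that lies in one direction.

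**3. Alpha divided over all four.** At two-sided 0.0125 each the bound is 4 × 0.0125 = 5%. If independent it is 1 − 0.9875⁴ = 4.9%.

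**4. Sample size, because any repair makes the smaller alpha binding.** For two means without baseline adjustment, n per group = 2(z_α + z_0.80)² / d², with d = 0.5 and z_0.80 = 0.842.
- One-sided 0.05, no split: 2(1.645 + 0.842)² / 0.25 = 49.5, so 50. This is the only simple variant tried that returns the stated 50.
- One-sided 0.025: 2(1.960 + 0.842)² / 0.25 = 62.8, so 63.
- Two-sided 0.025: 2(2.241 + 0.842)² / 0.25 = 76.0, so 77.
- Two-sided 0.0125: 2(2.498 + 0.842)² / 0.25 = 89.2, so 90.
- Attrition: 100 / 0.6 = 166.7, so 167. This reproduces.

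Power per test at 50 per group is Φ(0.5 × √(50/2) − z) = Φ(2.5 − z).
- Two-sided 0.025: Φ(0.259) = 60% (59% with the t distribution).
- Two-sided 0.0125: Φ(0.002) = 50% (49% with the t distribution).

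**The case against.** **A single test per subscale.** Section 6 opens by naming depression and anxiety as the primary outcomes, Section 9.3 analyses change over time in one model, and the success rule names no time. If one group-by-time test per subscale was meant, there are two tests at 0.025 and the total is at most 5%. This stands as a possible reading. However, the sentence with the split speaks of group differences at 8 weeks and 3 months, and nowhere does the article name a single test or a single primary time. The four-contrast reading is the more natural one, but it remains a reading.

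**Direction.** A reader might infer that the chance of a false efficacy claim is 7% to 9.5%. The article does not support that figure. Those rates count rejections favouring the waitlist, whereas the rule counts only a reduction. With two-sided tests the false-efficacy rate stays at or below 5%. This objection stands in full, and it is why both readings of sidedness are tabulated. It does not remove the problem, because 3.6% to 4.8% is well above 2.5%.

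**Three further inferences that do not belong here.**
- That efficacy could be claimed from a within-arm change: Section 2 predicts improvement relative to control and Section 6 uses between-group differences, so the rule is only loosely worded.
- That the winning result can be picked freely after the fact: both subscales and the either-rule are named in advance, so the issue is the number of chances.
- That daily functioning, part of the primary aim in Section 2, adds to the error: the WHO-DAS is outside the success rule and has no bearing on it.

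**Conclusion.** The concern holds as an inconsistency between Sections 4.1.4 and 6 over how many tests share the 0.05. On the most natural reading, four contrasts can satisfy the success rule and alpha is allocated for two, so the stated overall level is not controlled.

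The two-sided familywise error is about 7% to 9.5% over the assumed correlations. It comes close to 5% only when both correlations are about 0.9. The probability of a false efficacy claim is about 3.6% to 4.8% if 0.025 is two-sided and about 6.8% to 9.3% if it is one-sided. These figures rest on the assumed correlations and on four separate contrasts being tested. They do not apply if one test per subscale was intended.

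**What to change.** State that tests are two-sided. Define efficacy in Section 4.1.4 as a between-arm difference at 8 weeks on depressed mood or general anxiety. Test the two subscales with Holm at overall 0.05: the smaller p-value against 0.025 and, if that is met, the other against 0.05. Make both 3-month contrasts secondary. Carry the same wording into Sections 6 and 9.3.

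If both time points must stay confirmatory, apply Holm over all four contrasts, with a first step of 0.0125.

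**Cost.** The change is one of wording. Under the first option the 3-month result loses confirmatory status. Under the second, power per test falls further. At 50 per group and 0.5 SD, unadjusted for baseline, it is about 59% to 60% at two-sided 0.025 and 49% to 50% at 0.0125, against the 80% stated. Section 6 should restate the power under whichever option is chosen and give any baseline correlation relied on. Without such an adjustment, 80% per test needs 77 per group at 0.025 (154 / 0.6, so 257 recruited) or 90 at 0.0125 (180 / 0.6 = 300 recruited).

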## 5. Participant Timeline

Participant consent, screening, and assessment will take place online via a secure study-specific website hosted on the Black Dog Institute research platform (https://healthymind.blackdoghealth.org.au), which is separate from the intervention site. The research platform is password-protected; therefore, participants may require support from their helper during this component of the study. Once on the secure site, potential participants and their helper will complete the online screening questionnaire to establish eligibility. Eligible participants and their helper will then each provide informed consent online by reviewing and agreeing to the participation information and consent statement. After providing informed consent, eligible participants will be directed to a secure website where they will enter contact details and complete the baseline questionnaires with support from their helper, then complete the CBS Health cognitive assessment independently. To allow for participant fatigue, all online assessments can be paused and resumed at a later date. Ineligible participants will receive automated feedback explaining that the study is not right for them, based on their answers. Details of telephone counselling support (e.g., Lifeline) and other self-help and face-to-face resources will be provided as appropriate.

After baseline assessment, eligible participants will be randomly allocated to one of two conditions using computerised block randomisation at a 1:1 allocation ratio: (1) the intervention condition, in which participants have full access to the Healthy Mind program; or (2) the control condition, in which participants are placed on a waitlist and given access to Healthy Mind at the conclusion of the waitlist period. Subsequent assessment points coincide for both groups at post-intervention (8 weeks) and 3 months after randomisation. The full flow of participants is presented in Figure 4.

## 6. Sample Size

The primary outcomes for this study are depression and anxiety symptoms (measured using the ADAMS). Meta-analysis of psychological therapies for people with ID suggests an expected effect of treatment on similar measures of anxiety and depression symptoms of approximately 0.6 [43]. However, this is based on face-to-face treatments and may represent an overestimation [44]. To detect a more conservative effect size of ~0.5, we will need a minimum of 50 participants per group, therefore we will recruit a sample of approximately 167 individuals to allow for ~40% attrition. This calculation was based on the group differences on ADAMS between waitlist control and intervention groups at 8 weeks and 3 months, assuming 80% power and alpha = 0.05 (0.025 for each primary group difference), in order to detect a mean difference of 0.5 standard deviation units at 8 weeks and at 3 months.

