## Abstract

People with intellectual disability (ID) experience higher rates of mental illness and reduced access to appropriate care and treatment. Tailored electronic mental health (eMH) programs offer opportunities to address these disparities. The aim of this study is to examine whether a fully automated and self-guided eMH program tailored to the needs of people with ID can reduce symptoms of anxiety and depression and improve daily functioning in people with borderline-to-mild ID. Australians with borderline-to-mild ID, aged 16 years and older with mild-to-moderate depression and/or anxiety symptoms will be eligible to participate with the help of a nominated carer, if necessary. A randomised controlled trial with a sample size of 150 participants divided into treatment and waitlist control arms will be conducted. Participants randomised to the intervention group will have full access to the Healthy Mind program for eight weeks. The waitlist control group will gain full access to the program following the eight-week treatment period. Efficacy will be assessed on the Anxiety, Depression, and Mood Scale; Kessler-10; and the World Health Organisation Disability Assessment Schedule 2.0 across three time-points (baseline, eight weeks, and three months). We expect that people who use the intervention will report reduced depression and anxiety, relative to the control group. To our knowledge, this is the first study to examine the effectiveness of a fully automated eMH program for improving mental health in people with ID. We expect our study to render new knowledge on the delivery and effects of internet-based cognitive behaviour therapy (CBT) tools for people with ID.

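### Fifty per group gives about 59% power, not 80%, at the stated alpha of 0.025, and the Abstract's 150 recruits leave only 45 per group

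*Protocol article*

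**What the plan says.** Section 6 (Sample Size) gives the target: "To detect a more conservative effect size of ~0.5, we will need a minimum of 50 participants per group". The error rates are set by "assuming 80% power and alpha = 0.05 (0.025 for each primary group difference"), and the calculation is made "in order to detect a mean difference of 0.5 standard deviation units at 8 weeks and at 3 months". The basis is described as the difference between the two arms on the ADAMS at those two times. The section does not say whether the test is one-sided or two-sided. It gives no correlation between baseline and follow-up or between the two follow-up times.

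The section then allows for loss: "we will recruit a sample of approximately 167 individuals to allow for ~40% attrition". The Abstract gives another figure: "A randomised controlled trial with a sample size of 150 participants divided into treatment and waitlist control arms will be conducted". Section 8.1 sets 1:1 allocation, and Section 9.3 plans a linear mixed model for repeated measures, fitted by maximum likelihood.

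**The concern.** Section 6 prints both its inputs and its result, so the result can be checked, and a half-SD difference at alpha 0.025 ordinarily needs well over 50 per group. If 50 is too few, the trial claims a power that the printed inputs do not deliver.

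The gap matters because Section 6 chooses 0.5 as a cautious value, on the ground that the 0.6 seen with face-to-face treatment may be too high for an online program. If 50 per group has 80% power only for an effect above 0.6, that caution is lost. A null result would be read against a stated power of 80% when a true effect of 0.5 SD would be missed about four times in ten at each primary contrast.

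The two recruitment figures add to this: the lower one may not reach even the stated minimum.

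**Working it through.** **Inputs.** From Section 6: difference d = 0.5 SD (so SD = 1), power 80%, alpha 0.025 per primary difference, 50 per group, attrition about 40%, about 167 recruited. From the Abstract: 150 recruited. From Section 8.1: 1:1 allocation. Sidedness is not stated, so both readings are shown.

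**Step 1: the number per group.** The normal approximation is n = 2 × [(z for alpha + z for power) / d]², with z = 0.842 for 80% power. The t-based figure allows for the estimated SD.

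| Test | z for alpha | n per group, normal | n per group, t |
|---|---|---|---|
| Two-sided 0.025 | 2.241 | 2 × (3.083/0.5)² = 76.0 | 77.3, so 78 |
| Two-sided 0.05 (same as one-sided 0.025) | 1.960 | 2 × (2.802/0.5)² = 62.8 | 63.8, so 64 |
| One-sided 0.05 | 1.645 | 2 × (2.486/0.5)² = 49.5 | 50.2 |

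The plan's 50 matches only the last row. That row needs a one-sided test, which the text does not state, and no split of alpha, which contradicts the split that it does state.

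**Step 2: power with the stated 50 per group.** The expected test statistic is 0.5 / √(2/50) = 2.5.

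| Test | Power, normal | Power, t |
|---|---|---|
| Two-sided 0.025 | Φ(2.5 − 2.241) = 60.2% | 59.0% |
| Two-sided 0.05 (same as one-sided 0.025) | Φ(2.5 − 1.960) = 70.5% | 69.7% |
| One-sided 0.05 | Φ(2.5 − 1.645) = 80.4% | 79.9% |

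At two-sided 0.025, the smallest effect that 50 per group can detect with 80% power is d = 0.62.

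**Step 3: the attrition step.** 100 / (1 − 0.40) = 166.7, so 167 follows from 50 per group. If 78 per group is needed (156 in all), 167 recruits suffice only when attrition is at most 1 − 156/167 = 6.6%. At 40% attrition, 156 / 0.6 = 260 would have to be recruited.

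**Step 4: the Abstract's figure.** 150 × 0.60 = 90, or 45 per group. Power at two-sided 0.025 is then 53.8%, and the detectable effect is d = 0.66. The 150 would leave 50 per group only if attrition were at most 1 − 100/150 = 33.3%.

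**Step 5: could the planned model close the gap?** Adjusting for baseline multiplies the residual variance by 1 − ρ², where ρ is the baseline to follow-up correlation. The effective difference becomes 0.5 / √(1 − ρ²). At 50 per group, two-sided 0.025, t-based:

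| ρ (assumed) | Power |
|---|---|
| 0.3 | 64% |
| 0.5 | 73% |
| 0.6 | 80% |
| 0.7 | 89% |

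**Step 6: two time points.** With 50 per group, two-sided 0.025 at each time and an assumed correlation of 0.3 to 0.7 between the two test statistics (normal approximation), power to succeed at both times is 41% to 48%. Power to succeed at one or the other is 80% (79.6%) at 0.3, 76% at 0.5 and 72% at 0.7.

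**The case against.** The strongest reply is that the 59% belongs to an unadjusted t-test, which is not the planned analysis. The ADAMS is measured at baseline and the model in Section 9.3 can use it, so at a correlation of 0.6 or more the claimed 80% is met. A condensed article may leave such an assumption to a fuller document. Sidedness is also unstated and the hypothesis in Section 2 is directional, so 70% is a possible reading. Splitting alpha makes sense if success at either time counts, and that reading comes close to 80% when the two times are weakly correlated. Maximum likelihood also keeps people who are lost only at the later follow-up, so 40% attrition need not remove 40% of the information at 8 weeks.

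Much of this stands as a limit on the figures. The 59% and the 7% tolerable attrition are for an unadjusted two-sided test of completers, and the power for both times depends on how success is defined. A true power of 80% under the planned model is not ruled out.

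It does not rescue the text. Section 6 describes a plain between-arm difference in SD units and concludes 50 from it. The rescue needs a correlation of about 0.60, or a rule that either time suffices together with a low correlation, and Section 6 states neither. The fault is not a missing detail: the printed inputs and the printed result disagree. The one-sided reading also falls short of 80%.

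On recruitment, the word "approximately" does not cover a drop from 167 to 150, because 150 meets the stated minimum only if attrition is 33% or less.

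**Conclusion.** The concern holds, with high confidence. On the stated inputs the need is 78 per group, not 50. Fifty per group gives 59% power for a 0.5 SD difference at two-sided 0.025, and 70% if 0.025 is one-sided. No unadjusted comparison of the two arms at a single time point reaches 80% at the stated alpha. The Abstract's 150 contradicts Section 6's 167 and, at the protocol's own attrition, leaves 45 per group and 54% power.

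These figures assume a t-test on completers with equal group sizes and no gain from baseline or repeated measures, since no such gain is stated. If the baseline to follow-up correlation is about 0.60 or more, 50 per group is enough, but the calculation must then say so. The point should be corrected before the power claim is relied on.

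**What to change.** Change Section 6 in one of two ways:

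- **Restate the power.** Say that 50 completers per group give about 59% power for a 0.5 SD difference at two-sided 0.025, and 80% power for a difference of about 0.62 SD.
- **Base the calculation on the baseline-adjusted model.** State the assumed baseline to follow-up correlation and the reason for it. About 0.60 is needed for 80% power with 50 per group; 0.5 gives 73%.

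In either case, state whether the test is one-sided or two-sided. Use a single recruitment figure in the Abstract and Section 6. If it is 150, state that about 40% attrition leaves 45 per group, and give the power for that number (54% unadjusted).

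The cost is rewording two places. Under the first option the stated power becomes less favourable. Neither option needs extra participants or a change of design.

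### Sample size section: the only multiplicity rule stated is an equal Bonferroni split of 0.025 per primary difference; Holm's procedure on the same tests would give more power at the same 5% error (optional)

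*Protocol article*

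**What the plan says.** Section 6 (Sample Size) of the protocol article says: "This calculation was based on the group differences on ADAMS between waitlist control and intervention groups at 8 weeks and 3 months". It sets the error level and power in the same sentence, "assuming 80% power and alpha = 0.05 (0.025 for each primary group difference"), and gives the target effect: "in order to detect a mean difference of 0.5 standard deviation units at 8 weeks and at 3 months". The overall 5% is therefore divided equally between the two time points. The evaluable target is stated as "we will need a minimum of 50 participants per group".

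Section 9.3 (Statistical Analysis) names a mixed model for repeated measures but gives no test level and no step-down, recycling or hierarchical rule. Section 4.1.4 (Outcomes) counts the intervention as efficacious if either of two ADAMS subfactors, depressed mood or general anxiety, falls significantly. Section 6 does not say whether its two differences are taken once or once per subfactor.

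**The concern.** An equal split is valid but not the most efficient use of the 5%. Suppose p is 0.01 at 8 weeks and 0.04 at 3 months. Held at 0.025 each, the 3-month difference cannot be claimed. Under Holm it can, with the same overall error guarantee. What is at stake is power at each named time point, and power to show both, in a trial that expects about 40% attrition and has little power to spare.

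**Working it through.** **Inputs.** From Section 6: d = 0.5 SD at each time, 50 per arm, 80% power, overall alpha 0.05, 0.025 per difference. From Section 8.1: 1:1 allocation. Assumed, because not stated: two-sided tests, an unadjusted normal approximation, and a correlation of 0 to 0.9 between the 8-week and 3-month test statistics.

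**The plan's own figure.** n per arm = 2(z_alpha + z_0.80)²/d².
- Two-sided 0.025: 2(2.241 + 0.842)²/0.25 = 76.04, so 77.
- Two-sided 0.05, or one-sided 0.025: 62.8, so 63.
- One-sided 0.05 with no split: 49.5, so 50.

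The stated 50 is not reproduced at two-sided 0.025. The attrition step is right: 100/(1 − 0.4) = 167.

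**Power of one comparison at 50 per arm.** The expected z is 0.5 × √(50/2) = 2.5.
- At two-sided 0.025: Φ(2.5 − 2.241) = 60.2%.
- At two-sided 0.05: Φ(2.5 − 1.960) = 70.5%.

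**Why Holm cannot lose on the same two tests.** Holm tests the smaller p-value at 0.025 and, only if that is significant, the other at 0.05. Anything with p ≤ 0.025 is still rejected. The extra rejections at one time point are the cases where its own p lies between 0.025 and 0.05 and the other p is at most 0.025. If both null hypotheses are true, a false claim still needs the smaller p to reach 0.025. If only one is true, it is tested at no more than 0.05. The family-wise limit is 0.05 under any dependence.

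**Check by hand at correlation 0.**
- Gain per time point: 0.602 × (0.7054 − 0.6020) = 0.062, so 60.2% becomes about 66.4%.
- Both: 0.602² = 36.2% becomes 36.2% + 2 × 6.2% = 48.7%.

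**Simulation** (1,000,000 draws per setting; 50 per arm; 0.5 SD at both times):

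| Correlation | Each time: split → Holm | Both: split → Holm | At least one (either rule) |
|---|---|---|---|
| 0 | 60.2% → 66.5% | 36.3% → 48.7% | 84.3% |
| 0.5 | 60.2% → 65.6% | 44.1% → 55.0% | 76.3% |
| 0.7 | 60.2% → 65.3% | 48.0% → 58.1% | 72.5% |
| 0.9 | 60.2% → 64.5% | 53.4% → 61.9% | 67.2% |

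The gain shrinks as correlation rises, so correlation is not its source. With no effect at either time, the family-wise error is the same for both rules (4.9% at correlation 0, 3.6% at 0.9). For 80% power at each time point, the split needs 77 per arm and Holm about 67 to 71.

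**If the 3-month effect is small.** The 8-week gain is largest at correlation 0, where it equals the 3-month power at 0.025 times 0.1034.
- 3-month effect 0: 0.025 × 0.1034 = 0.3 points.
- 3-month effect 0.25 SD: about 0.160 × 0.1034 = 1.7 points.

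At correlation 0.9 both gains are close to zero.

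**If there are four primary tests** (two subfactors × two times). At 0.025 each the error limit is 4 × 0.025 = 0.10, or 1 − 0.975⁴ = 0.096 if independent. To hold 0.05, Bonferroni uses 0.0125 and per-test power is Φ(2.5 − 2.498) = 50%. Holm over all four, with 0.5 SD throughout, time correlation 0.5 to 0.7 and subfactor correlation 0.5 (all assumed), gives about 59%. The chance of at least one rejection is 79-82% under both of these rules.

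**The case against.** Five points can be made for the plan.

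- **The 0.025 is a planning level.** It stands in the sample size section, and 0.025 is also Holm's first step. A reader might infer that the trial has committed itself to testing each difference at 0.025 whatever the other shows. The document does not say that, and an analysis plan not shown here could name a step-down rule. This stands as a limit. It remains true that the equal split is the only rule the public text gives.
- **Four tests change the comparison.** A reader might infer that Holm beats the stated 0.025 however many primary tests there are. It does not: Holm over four starts at 0.0125, and per-test power is then about 59% against 60% at an uncontrolled 0.025. Holm's advantage is over Bonferroni on the same family. This objection stands in full.
- **The favourable case assumes 0.5 SD at both times.** That is the plan's own assumption. But Section 3 gives controls access after 8 weeks, while Section 4.1.3 gives it after the three-month survey. Those passages must be reconciled. If controls are treated before the 3-month assessment, that contrast may shrink and most of the 8-week gain goes with it.
- **The success rule is of the either kind.** Holm never changes the chance of at least one significant result, and no section requires both differences. This also stands.
- **Bonferroni has matching intervals.** For two tests, every difference that only Holm rejects has p between 0.025 and 0.05, so its 97.5% interval includes zero. This is a real cost of the change.

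**Conclusion.** The point holds as an optional efficiency improvement. For two tests, 50 per arm and 0.5 SD at both times, the equal split gives up about 4 to 6 points of power at each time point and about 8 to 12 points for showing both, with no gain in error control. This rests on two-sided tests, a normal approximation and an assumed correlation of 0 to 0.9.

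Two stronger conclusions are not supported. The first is that the split is inefficient because the repeated measures are correlated: Holm does not use the correlation, and its advantage is largest when there is none. The second is that Holm would rescue the sample size: 64-67% is still well short of the stated 80%, and the mismatch between 50 per arm and two-sided 0.025 (77 needed on an unadjusted comparison) is the larger fault in the same paragraph.

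**What to change.** State, in the protocol or the analysis plan, that the primary group differences are tested with Holm's procedure at an overall two-sided alpha of 0.05, and list every test in the family. If the family is one ADAMS comparison at each of two times, Holm starts at 0.025. If it is two subfactors at two times, Holm must cover all four and start at 0.0125.

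Report Holm-adjusted p-values. If simple Bonferroni-level intervals are shown beside them (97.5% for two tests), add a note that these will include zero for differences that only Holm rejects.

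The cost is a sentence or two, with no extra participants or data, and less simple agreement between intervals and tests. The sample size needs its own correction, which this change does not supply.
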